#### 6.4 RANDOMISATION

Central randomisation can be performed by the investigator or by a delegate or by the medical team member (from NICU). Infants assessed as eligible will be randomised to control group or intervention group using variable block randomisation stratified for gestation age (< 26 weeks and ≥ 26 weeks) and study site using web based secure software (REDCap). Randomisation codes for the study will be generated by biostatistician ([name] has generated the codes). Permuted blocks will maintain group balance, infants will be allocated to two groups in a 1:1 ratio. Multiple births (twins) will be assigned to the same arm of the treatment (either intervention or control). Multiple births (twins) will be randomised to the same group, based on negligible intra-class coefficient (ICC) burden of hypoxia within pairs of twins in SafeBoosC-II study (16) and survey of parents of multiple births (19).

To ensure concealment, the block sizes will not be disclosed. Additionally, allocation concealment will be ensured, as REDCap will not reveal the randomisation until the infant has been recruited into the trial.

REDCap will maintain a list of participants enrolled. Each site PI will access only to their site records. The chief investigators will have access to all sites to oversee enrollment. Participants will be given unique codes to protect their identity on all documentation utilised for recording and analysis purposes. Separate data records will be maintained for re-identifiable and de-identified data.

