## **PATIENT POPULATION**

### *Inclusion criteria*

- Preterm infants (singleton or twin births) <29 weeks gestation who are either inborn (born at the local study site hospital) or outborn (born outside the local study site hospital) and less than 6 hours of age when admitted to the study site NICU.

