## **SAMPLE SIZE**

Based on the results of the Safe-BoosC-II study, a 50% reduction in mean burden of hypoxia and hyperoxia in active treatment relative to control would be considered worthwhile. This corresponds to a reduction of 0.3 in the mean of log-transformed burden of cerebral hypoxia and/or hyperoxia. In the Safe BoosC-II study, a 58% reduction was achieved. Assuming a standard deviation of 0.5 in log-transformed burden, this would require 45 babies per group to achieve 80% power at 5% two-sided alpha. To account for the clustering effect of twins being allocated to the same treatment, we assume that 30% of babies are twins-based on regional incidence of twin births (giving an average cluster size of 1.3, and a within-twin correlation of 0.1 in the outcome. This gives a design effect of 1.03 by which the sample size is adjusted, leading to a sample size of 47 per group, 94 babies in total. We aim to recruit 100 babies to account for some loss to follow-up or missing data. For consented participants, if the NIRS monitoring was discontinued earlier than 5 days after birth, data collected until discontinuation of monitoring will be used for analysis of the primary outcome.

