### *Analysis of the outcomes*

Participant demographic and clinical characteristics and study outcomes will be presented using standard descriptive statistics: frequencies and percentages for categorical variables, mean, standard deviation and range or median, quartiles and range for continuous variables. All efficacy analyses will be performed according to randomized treatment. We will use a suitable transformation to ensure normality for the primary outcome, the burden of cerebral hypoxia and hyperoxia and use generalized estimating equation (GEE) or a similar method for comparison between groups. Sub-group analysis for stratification variables will be performed. For reporting the burden of cerebral hypoxia and hyperoxia, we will include deviations in cerebral oxygenation more than a minute. This pragmatic approach will ensure we achieve a balance between responding to an alarm from poor sensor contact with the participant and identifying true real-time changes in cerebral oxygenation. To allow comparison of the primary outcomes with other studies, we will also report the burden of cerebral hypoxia and hyperoxia more than 10 minutes. Other study outcomes will be compared using similar methods, using GEE methods with normal or binary outcome distribution and correlation between outcomes in twins. Adjusted models will explore predictors out outcomes. No corrections for multiple hypotheses will be performed. Adjusted models will be used to explore predictors of outcomes. Variables that differed significantly between the two groups, and could plausibly contributory to the outcome, will be considered for adjustment. A fixed adjustment for gestational age category will be included as an a priori specified variable. For this trial, no imputation of missing data will be performed and sensitivity analysis will only be performed separately for the burden of cerebral hypoxia and cerebral hyperoxia. In future, sensitivity analysis may be performed for variables such as specific gestational age or treatment received.

Withdrawn participants will be replaced in the study with new randomisation (per protocol). To facilitate and ensure long term follow up, existing measures which are standard practices includes providing appointment letters by post, reminding and confirming with families by phone and/or text message when follow up appointment is close to date.

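### Gestational age is pre-specified as a covariate only in two categories; adding its exact value would recover a small amount of precision at almost no cost

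*Combined protocol and SAP*

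**What the plan says.** The SAP, under Analysis of the outcomes, fixes one covariate beforehand: "A fixed adjustment for gestational age category will be included as an a priori specified variable". It does not define the categories there. The only ones in the documents are the randomisation strata, given in Protocol 6.2 and 6.4 and in the SAP synopsis and randomisation section. In Protocol 6.4 the wording is "using variable block randomisation stratified for gestation age (< 26 weeks and ≥ 26 weeks) and study site".

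Three other statements in the same SAP section bear on the point:

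- Further covariates are chosen from the data: "Variables that differed significantly between the two groups, and could plausibly contributory to the outcome, will be considered for adjustment".
- Exact gestational age appears only as a later possibility: "In future, sensitivity analysis may be performed for variables such as specific gestational age or treatment received".
- The purpose of adjustment is put as "Adjusted models will be used to explore predictors of outcomes". This leaves open whether the fixed adjustment belongs to the primary GEE comparison or only to exploratory models. Protocol 9.3 names no covariate for the primary comparison.

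No section says outright that exact gestational age is recorded. It follows in practice from the upper limit for entry ("Preterm infants (singleton or twin births) <29 weeks gestation who are either inborn"), from strata written in weeks and days in Protocol 6.2, and from the possible future analysis just quoted.

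**The concern.** The plan treats gestational age as prognostic: it stratifies on it and makes it the one pre-specified covariate. A two-level version then treats all infants below 26 weeks as alike, and likewise all those from 26+0 to 28+6. Two things follow.

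First, prognostic information the trial should already hold goes unused, and chance differences between arms within a stratum are left uncorrected. Twins share an arm and normally share a gestational age, which makes such differences somewhat larger.

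Second, the rule on variables that differ significantly between groups means exact gestational age could enter the model, or not, according to a test on the observed data. Pre-specifying it closes that route.

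At stake is some width in the confidence intervals for burden and for the continuous secondary outcomes. The validity of the comparison is not in question.

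**Working it through.** **1. The plan's sample size.** Inputs from the SAP, Sample size: difference 0.3 ("This corresponds to a reduction of 0.3 in the mean of log-transformed burden of cerebral hypoxia and/or hyperoxia"; log10 of 0.5 is −0.301), SD 0.5, 80% power, two-sided 5%. The normal formula gives 44 per group and the noncentral t gives 45, as stated. Then 45 × 1.03 = 46.35, rounded up to 47 per group, 94 in total. The plan reproduces, and it contains no allowance for covariate adjustment.

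**2. Share of the gestational-age signal that the cut keeps.** This share, k, is the between-category variance divided by the total variance of the gestational-age effect. If gestational age is uniform up to 29 weeks and its effect is linear, k = 3p(1 − p), where p is the share of infants below 26 weeks.

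- From 23 weeks: p = 0.50, k = 0.750, 25% lost.
- From 22 weeks: p = 4/7, k = 0.735, 26% lost.
- From 24 weeks: p = 0.40, k = 0.720, 28% lost.

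Fifteen rising or bell-shaped distributions, also with a linear effect, lose 26–36% in fourteen cases and 45% in one. The distributions and the lower limits of 22–24 weeks are assumptions, because the documents give neither.

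The shape of the effect matters more. With a uniform 23–29 weeks distribution, the loss is 0% for a step at 26 weeks, 8% for a steep sigmoid centred there, and 39–59% when the effect is concentrated at the lowest gestations.

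**3. What that costs in power.** Let R² be the share of outcome variance explained by exact gestational age (assumed). Residual SD is 0.5√(1 − kR²) with the category and 0.5√(1 − R²) with the exact value. Power uses the noncentral t with 47/1.03 = 45.6 effective infants per arm. Example at R² = 0.10, k = 0.75: SDs 0.481 and 0.474, noncentrality 2.98 and 3.02. The variance ratio is (1 − kR²)/(1 − R²) = 0.925/0.90 = 1.028.

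| R² | Power, category (25% lost) | Power, category (36% lost) | Power, continuous | Variance ratio (25% lost) |
|---|---|---|---|---|
| 0.05 | 82.4% | 82.2% | 82.9% | 1.013 |
| 0.10 | 83.8% | 83.4% | 84.8% | 1.028 |
| 0.20 | 86.7% | 85.9% | 88.7% | 1.062 |
| 0.30 | 89.6% | 88.4% | 92.3% | 1.107 |

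With no gestational-age adjustment at all, power is 80.9%. The gain from the exact value is 0.5, 1.0, 2.0 and 2.7 points down the table at 25% lost, and 0.7, 1.4, 2.8 and 3.9 points at 36% lost.

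**4. Cost of the extra term.** Keeping the stratum and adding the continuous value uses one more degree of freedom, which inflates variance by roughly 1/90, or 1.1% (94 infants less four parameters). The table does not deduct this. At a correlation of 0.2 (R² = 0.04) the gain is 0.97/0.96 = 1.010, so nothing is left. At R² = 0.05 almost nothing is left.

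**5. Chance imbalance within strata.** With uniform gestational age from 23 weeks, the SD within a stratum is 3/√12 = 0.866 weeks. For 100 infants, the SD of the difference between arms is 0.866 × √(4/100) = 0.173 weeks. If twins share a gestational age and 30% of babies are twins (the SAP's figure), multiply by √1.3 = 1.140 to get 0.197. About one trial in 20 would exceed 1.96 × 0.197 = 0.39 weeks, under three days. With SD 0.5, a gestational-age SD of 6/√12 = 1.732 weeks and a correlation of 0.3–0.5, the slope is 0.087–0.144 log units per week. That difference therefore shifts the comparison by 0.03–0.06, against a target of 0.3.

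**The case against.** The strongest reply is that nothing here is wrong. Adjusting for the stratum is valid, leaves the comparison unbiased and matches the randomisation; the exact value is an efficiency preference. That stands.

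A reader might infer that a quarter of the available information is thrown away. The documents do not support this. The figure needs a near-uniform distribution and a linear effect, and it is a share of gestational age's own explained variance, not of precision or sample size. The primary outcome also pools two opposite deviations, hypoxia and hyperoxia, so even a monotone relation with gestational age cannot be taken for granted. For a symmetric U-shape around 26 weeks, neither the category nor a straight line would help.

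A reader might also infer that the trial has no precision to spare. That too is unsupported: 94 infants suffice without any covariate gain, and 100 are to be recruited. The standard error already reflects chance imbalance of the size in step 5.

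Adding terms everywhere would carry a cost of its own. Table 1 of the protocol gives mortality of 32/166 in the earlier trial, or about 19 deaths per 100 infants. Treatment plus stratum, linear and quadratic terms would leave about five events per parameter. This objection stands and shapes the recommendation.

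One part of the reply is weaker. The plan does allow exact gestational age to enter through the rule on significant differences or in a future analysis, but both routes are discretionary. Neither replaces a pre-specified term.

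**Conclusion.** The point holds as a small improvement in efficiency. The one pre-specified covariate is in two levels, and the exact value should be on file. If the effect is roughly linear, the category loses about 25–35% of gestational age's own explained variance. For other shapes the loss runs from nil to well over a third.

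At a quarter lost, the gain in power is about 0.5–1 point at R² of 0.05–0.10 and 2–3 points at 0.20–0.30, before the roughly 1% variance cost of the extra term. At a correlation of 0.2 or less the gain is negligible. In infants, the ratios 1.028 and 1.062 correspond to about 3 and 6 per 94, comparable with the six recruited above the requirement. All of this depends on R² and on a distribution that the documents do not give.

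Planned power and validity are not in doubt. The change is worth making because it costs little and removes a data-dependent choice. Which model the fixed adjustment belongs to must be settled in any case.

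**What to change.** Amend the SAP, Analysis of the outcomes, before unblinding:

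- State that the primary GEE comparison, and the models for continuous secondary outcomes, adjust for gestational age at birth in weeks and days as a continuous covariate, together with the gestational-age stratum (below 26 weeks; 26 weeks or more). Keeping the stratum stays consistent with the randomisation and guards against a step at 26 weeks.
- Add a check for curvature as a sensitivity analysis.
- In binary models with few events, use continuous gestational age in place of the category, so that no parameter is added.
- Keep the two categories for the planned subgroup display.

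The cost is a few lines of SAP text, one degree of freedom in the continuous-outcome models and an assumption of approximate linearity over the eligible range. No new data are needed, provided gestational age is stored in weeks and days, which should be confirmed. Adjustment for site, the other stratification factor, is a separate question that this change does not settle.

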### 4.3 BACKGROUND INFORMATION

Background and introduction:

Premature babies are very fragile and vulnerable, especially those born less than 29 weeks gestation. They are at a greater risk of death, cerebral palsy, intellectual impairment, learning disorders, vision and/or hearing loss (1-3). In 2017, approximately 1600 premature infants < 29 weeks gestation age were born and admitted to neonatal intensive care units in Australia and New Zealand. This is a vulnerable, high risk group with a combined adverse outcome incidence of ~33% (for rates of mortality and moderate to severe functional impairments) (4).

The risk of cerebral palsy is high in extremely preterm babies (12% vs 1% in term born) (5). There are significant expenses to the family and associated economic impact in caring for a child with cerebral palsy, estimated at \$43,431 per annum and up to \$115,000 if loss of wellbeing is

considered (6). The mechanism of brain injury in extremely preterm infants is multi-factorial. One proposed mechanism is the immature brain is exposed to periods of low oxygen (cerebral hypoxia) and/or periods of high oxygen (cerebral hyperoxia).

Large multi-site randomised controlled trials comparing lower (85-89%) versus higher (91-95%) peripheral saturation target ranges in extremely preterm infants found increased risk of mortality and neonatal morbidities for infants outside target range, but the trials did not identify differences in neurodevelopmental outcomes, including cerebral palsy (7-13). Cerebral near infra-red spectroscopy (NIRS) monitoring is a safe, non-invasive optical technology that allows assessment of tissue oxygenation of the brain (14), thus providing a non-invasive measure of the blood flow to the brain.

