### Outcomes

| Tool                 | Outcomes                                                                                                                                            | Time points                                                                   |
|-----------------------------|------------------------------------------------------------------------------------------------------------------------------------------------------------|--------------------------------------------------------------------------------------|
| Cerebral NIRS monitors      | Burden of hypoxia and hyperoxia expressed as percentage time spent < 65% and > 90%.                                                                        | First 5 days of monitoring period                                                    |
| Medical records             | Mortality rates                                                                                                                                            | Prior to home discharge                                                              |
| Cerebral imaging            | Evidence of brain injury on cranial ultrasounds and MRI brain (when performed for clinical reasons)                                                        | Prior to home discharge                                                              |
| Medical records             | Presence of neonatal morbidities (chronic lung disease, necrotizing enterocolitis, retinopathy of prematurity)                                             | Prior to home discharge                                                              |
| Neuro-developmental testing | 

General movement assessment

Cognition, motor and language domain scores on Bayley Scales of Infant

 | At 4 months (CGA)

At 12 months (CGA), 18-24 months (CGA), and 5 years of age. |

|                                 |                                                                                                                                  |                                   |
|---------------------------------|----------------------------------------------------------------------------------------------------------------------------------|-----------------------------------|

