|                                 | and Toddler development 
 
• Wechsler Preschool and Primary Scale of Intelligence
 
 | 5 years of age                    |
| Pulse oximeter, medical records | pulse oximetry (SpO 2 ), heart rate (HR) and blood pressure                                                           | First 5 days of monitoring period |
| Medical records                 | Serious and non-serious adverse reactions                                                                                        | First 5 days of monitoring period |

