**Below is a list of expected serious adverse events in premature babies born at this gestational age:**

- Death before hospital discharge
- Serious early and/ late onset sepsis
- Major intra-ventricular haemorrhage
- Neonatal chronic lung disease
- Pulmonary air leaks
- Advanced necrotising enterocolitis
- Peri-ventricular leukomalacia (PVL) or diffuse white matter loss
- Advanced retinopathy of prematurity
- Sensorineural hearing loss
- Cerebral palsy
- Moderate to severe functional impairment.

Serious adverse events which may be life threatening are common in preterm infants, however, the proportion of **unexpected serious adverse events** (in the opinion of the investigator) is expected to be small.

AN **UNEXPECTED SERIOUS ADVERSE EVENT**(SAE) is any untoward medical occurrence that is not expected and:

- results in death, or
- is life-threatening (i.e. the subject is at risk of death at the time of the event), or
- requires prolongation of hospitalisation, or
- results in persistent or significant disability or incapacity

or

- other important medical events which, in the opinion of the investigator, are likely to become serious if untreated

NOTE: The term “life-threatening” in the definition of “serious” refers to an event in which the baby was at risk of death at the time of the event; it does not refer to an event which hypothetically might have caused death if it were more severe.

**The investigator is responsible for reporting all Unexpected Serious Adverse Events occurring during the study to the CI’s within 1 working day by email.** The Trial Management Committee (TMC) all other Principal Investigators participating in the study will be informed. The investigator or delegate at each participating institution is responsible for reporting unexpected serious adverse events to their HREC.

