## **STATISTICAL ANALYSIS**

Analysis will be conducted per-protocol using RStudio.Version(4) at a significance level of 0.05 with a two-sided alternative hypothesis. The reporting will adhere to the CONSORT guidelines.

Data cleaning: In absence of international guidelines on handling NIRS artifacts, the artifacts will be included in the data analysis. Extreme values for cerebral oxygenation (0 and 100) will be removed.

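### With no imputation and no scoring rule for untestable survivors, the most impaired children drop out of the exploratory Bayley and Wechsler comparisons, which can bias the arm difference in either direction

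*Combined protocol and SAP*

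**What the plan says.** The SAP (Statistical Analysis, Analysis of the outcomes) sets one missing-data rule for the whole trial: "For this trial, no imputation of missing data will be performed". The same sentence confines sensitivity analysis to looking at hypoxia and hyperoxia separately. The possible future analyses it mentions concern gestational age and treatment received, not missing scores. Outcomes other than the primary are to be compared by GEE with a normal or binary distribution, allowing for twins.

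The Outcomes table in protocol section 6.5 gives neurodevelopment as test results: "Cognition, motor and language domain scores on Bayley Scales of Infant" and Toddler Development at 12 months, 18-24 months and 5 years, and the "Wechsler Preschool and Primary Scale of Intelligence" at 5 years. General movements are assessed separately. Section 5.4 classes all of these as exploratory secondary outcomes.

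Neither document gives a lowest score, an impairment category or a reason-not-tested item for a child who is seen but cannot complete the test. The SAP's rule for monitoring that stops early (Sample size section) covers only the primary outcome.

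**The concern.** A child without a score cannot enter a GEE on scores. For a surviving child who attends but cannot be tested because of severe motor, cognitive or sensory impairment, the outcome is in substance known and very poor. The plan nevertheless offers no route into the analysis except as a missing value, and missing values are left out.

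This missingness is informative. It follows from the injury that the intervention is meant to reduce, so the share of untestable children may itself differ between arms. If the intervention spares children from untestability, the available-case comparison misses that benefit. If it increases severe impairment, the comparison misses that harm.

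The population makes this more than a remote case. Section 4.3 says "The risk of cerebral palsy is high in extremely preterm babies (12% vs 1% in term born"), and section 8.2 lists "Moderate to severe functional impairment" among the expected serious adverse events. At stake is the reading of the Bayley and Wechsler results. The primary conclusion on burden is not at stake.

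**Working it through.** **What the plan's own figures cover.** The SAP's sample size rests on a 0.3 reduction in log burden with SD 0.5: "this would require 45 babies per group to achieve 80% power at 5% two-sided alpha". The normal formula gives 2 × (0.5 × (1.96 + 0.84) / 0.3)² = 43.6 per group. The t-test version gives 44.6, so 45. The design effect is 1 + 0.3 × 0.1 = 1.03, and 45 × 1.03 = 46.35, so 47 per group and 94 in total, with 100 recruited. The figure reproduces, but it concerns burden only. The documents give no SD, effect, untestable rate or 5-year loss rate for Bayley or Wechsler, so what follows rests on assumptions.

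**Inputs**
- Survivors per arm: 40. With 50 randomised per arm and the earlier phase II trial's mortality (section 4.3, Table 1: 12/86 and 20/80), survivors would be about 43.0 and 37.5, with mean 40.3.
- Tested mean M = 90, SD 15, floor score F = 50: assumed.
- Untestable share in control u = 3%, 6% or 12%: assumed. The top value is the cerebral palsy rate in section 4.3, taken as an upper bound because not every child with cerebral palsy is untestable.
- The intervention halves the share, and spared children score like the others: assumed.

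**Formulas.** The available-case mean is M in each arm, so the analysis as written shows a difference of 0. With floor scoring, the arm mean is (1 − u)M + uF. The difference the analysis misses is therefore (u − u/2)(M − F) = (u/2) × 40.

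With floor scores the variance in an arm is (1 − u) × 15² + u(1 − u) × 40². The standard error of the difference is the square root of the sum of the two arm variances divided by 40. The available-case standard error is 15 × √(1/[40(1 − u)] + 1/[40(1 − u/2)]).

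| Control untestable | Control mean, floor-scored | Intervention mean, floor-scored | Missed difference | SE, available-case | SE, floor-scored |
|---|---|---|---|---|---|
| 3% | 88.8 | 89.4 | 0.6 | 3.4 | 3.6 |
| 6% | 87.6 | 88.8 | 1.2 | 3.4 | 3.8 |
| 12% | 85.2 | 87.6 | 2.4 | 3.5 | 4.1 |

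The missed difference is 0.17, 0.32 and 0.59 of the floor-scored standard error. Twin clustering would multiply the standard errors by √1.03 ≈ 1.015, which changes little.

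**Direction.** If the control and intervention shares are exchanged, the same 0.6 to 2.4 points become a missed harm. More generally, let d be the difference among tested children, g the distance of the floor below the tested control mean (both in SD units), and uI and uC the untestable shares. The all-survivor difference is (1 − uI)d − (uI − uC)g. Equal shares only shrink d: 0.2 SD becomes 0.19 at 5% and 0.18 at 10%. The bias that matters comes from unequal shares.

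**The case against.** **The exclusion is inferred.** The SAP does not say that untestable children are excluded. It bars imputation and is silent on these children. A preset lowest score is an endpoint definition and would not conflict with that rule. This stands as a point about wording, and it shows the repair is compatible with the SAP. It does not remove the gap: without a preset rule, the child has no score, and a floor chosen after the data are seen would be a post hoc decision.

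**Severe outcomes appear elsewhere.** Mortality and brain injury are separate outcomes. Cerebral palsy and functional impairment are listed as expected serious adverse events. So severe cases do not disappear from the trial. But those last two have no planned comparison between arms, and the loss from the score comparisons remains.

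**A reader might infer that the sign of the effect would reverse.** An example can be built. Of 40 per arm, let 4 control and 2 intervention children be untestable, with the two spared children scoring 60. The available-case difference is (36 × 90 + 2 × 60)/38 − 90 = −1.6. With floor scores it is 86.5 − 86.0 = +0.5. The documents do not support a claim of this kind. Every input is assumed, and the standard errors are about 3.6 and 4.1, so the 95% limits are roughly ±7 and ±8 points. Neither figure says anything about direction.

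**A reader might also infer that children lost by 5 years are absent from all these comparisons.** They are not. Bayley is also scored at 12 and 18-24 months, so a child lost after 2 years is missing only from later assessments. Ordinary loss is also a different problem: if it is unrelated to the score given arm and covariates, it costs precision but need not bias. Sections 4.3 and 8.4 describe routine follow-up to 5 years, although no retention rate is given.

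**Floor scoring has costs.** It skews the scores and raises the SD. At 10% untestable, the control SD rises from 15 to 18.6. It also leaves deaths open. The earlier trial's rates imply about 7 and 12 to 13 deaths per 50, probably a larger group without scores. Both points stand and are met in the fix.

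**Conclusion.** The concern holds in a limited form. The trial-wide no-imputation rule, the absence of a scoring rule for untestable survivors, and the absence of any sensitivity analysis for neurodevelopment together leave an available-case comparison whose missingness is informative. The bias can run either way.

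Under the assumed inputs it is about 0.6 to 2.4 points, against a standard error of about 3.5 to 4. That is modest, and no statement about sign is justified. The size depends on the assumed mean, floor, untestable shares and halving, none of which the documents give. The outcomes are exploratory and the burden result is unaffected. The change is still worth making before unblinding, because a preset rule is cheap and handles these children better than leaving them out.

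**What to change.** In the SAP, for the Bayley and Wechsler outcomes:

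1. Assign a child who is seen but cannot be tested because of severe impairment the test's preset lowest score, and count that child as severely impaired in a binary comparison between arms.
2. Record the reason for non-testing on the existing electronic data sheet, and report missingness by arm and reason.
3. Show the available-case result as a sensitivity analysis, and add a rank-based or robust check because floor scores add skew and raise the SD.
4. State separately how deaths before assessment are handled.

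For children lost to follow-up, a sensitivity analysis using earlier scores is optional. With about 40 children per arm and different instruments at different ages, multiple imputation or a repeated-measures model is a trade-off and should not be required. The no-imputation rule can stay for the primary outcome.

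The cost is SAP wording and one data field, with no new visit, test or participant. The downside is some loss of precision in the score comparison.
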